### Eligibility criteria {10}

#### General eligibility criteria

Eligibility will be assessed during the intake by study team members trained in administering the MINI International Neuropsychiatric Interview 5.0.0 (M.I.N.I.; [69]). The inclusion criteria are as follows:Age between 18 and 65.Diagnosis of unipolar or bipolar depression (seasonal or non-seasonal) confirmed by the M.I.N.I. [69].Currently experiencing a depressive episode, as indicated by a Quick Inventory of Depressive Symptomatology Self-Report (QIDS-SR; [70]) score of 6 or higher.Proficiency in either Dutch or English is required for questionnaire completion.

Participants are excluded from participation if they:Are currently experiencing a (hypo)manic or mixed episode, as determined by the M.I.N.I. assessment [69].Are presently in a psychotic episode, as determined by the M.I.N.I. assessment [69].Exhibit significant active suicidality, indicated by a score of 10 or higher on the M.I.N.I. module [69].Initiated antidepressant therapy (including medication, psychotherapy, BLT, or other specific depression treatments) within the last 2 months prior to study enrolment.Have a bipolar disorder but are currently not under mood-stabilizing treatment for at least 1 month at the recommended dosage.Have used melatonin or agomelatine in the past month.Are currently using antibiotics.Are currently taking medications that increase light sensitivity.Have travelled across more than one time zone in the past month or during the treatment period.Have travelled to sunny holiday destinations or engaged in outdoor winter sports in the past month.Have pre-existing eye and skin disorders such as retinitis pigmentosa, porphyria, chronic actinic dermatitis, and sun-induced urticaria.Have systemic disorders with potential retinal involvement, such as rheumatoid arthritis and systemic lupus erythematosus.Have color blindness (based on self-report).Worked night shifts within the last three months.Suffer from (retinal) blindness, severe cataracts, or glaucoma.Experience light-induced migraine or epilepsy.Are currently pregnant or have a child Younger than 18 months old.

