### Justification for the saliva sampling sample size

Saliva sampling is optional in the study protocol to reduce participation barriers. The main aim of the saliva sampling is to compare possible shifts in DLMO between conditions. A simulated dataset was created using the *simr* package in R, with a mean DLMO set at 23:00 and extensive between-person variance (*SD* = 120 min) and within-person variance (*SD* = 45 min). Using a mixed-effects model with a random intercept for participants, we simulated a sample of 72 participants measured at two timepoints (pre- and post-treatment). The analysis yielded a power of 96.40% (95% CI 95.05, 97.47) to detect a phase shift of 30 min in DLMO with an alpha level of 0.05. This high power suggests that even with the optional saliva sampling and a sample size of 72 we can confidently assess the effect of BLT on circadian rhythm changes.

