### Recruitment {15}

We intend to include participants year-round for approximately 2 years. The distribution of the recruitment burden is shared between two mental health clinics: GGzE’s aim is to include 171 participants, while LUBEC aims for 60. At GGzE, all individuals referred for BLT are approached for potential participation. Previous light therapy studies conducted at this center with the same enrolment strategy have achieved inclusion rates of approximately 100 participants per year. Given that this study is considered more extensive than previous research, we anticipate it will take approximately 2 years to reach the targeted enrolment of 171 participants. At LUBEC, BLT is offered for the first time, and only in conjunction with study participation. Recruitment efforts involve the collaboration with primary care and secondary mental health institutions for the referral of patients.

The rate of participant accrual is reviewed every half year. The number of participants who consented but did not qualify and the number of qualified, enrolled participants who dropped out will also be examined to detect patterns of insufficient recruitment rates. These will be addressed with modified recruitment strategies so that we can meet our recruitment goals.

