#### Treatment effects on sleep parameters

To analyze changes in sleep patterns over time and between treatment conditions, multilevel mixed-effects models will also be utilized. Sleep outcomes include the following outcomes from both sleep diaries and actigraphy: sleep duration, sleep onset latency, wake after sleep onset, midsleep timing, sleep onset, and sleep offset. Additionally, sleep quality will be calculated from sleep diary and sleep fragmentation from actigraphy. The fixed effects structure will encompass time (*days since treatment start*), and the interaction between time and treatment condition (*Light@Home*,* LightCafé*, and* LightCafé* +), allowing us to explore how sleep patterns evolve throughout the intervention and whether these changes differ across conditions. The inclusion of random intercepts for participants and study centers, along with random slopes for time within participants, will be evaluated based on model fit criteria. Additionally, the model will incorporate a factor indicating whether a day is a weekend or weekday to account for social jet lag experienced by participants.

Furthermore, we will investigate the relationship between subjective sleep measures from sleep diaries and objective data obtained from actigraphy through correlation analyses. Next, we will assess the total PSQI and ISI scores over time and between conditions using a linear mixed model approach as described above, focusing on the timepoints of *Baseline, 4 weeks post-treatment, 10 weeks post-treatment*, and *4 months post-treatment* instead of *days since treatment start.*

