#### Circadian effects of BLT and their relation to the antidepressant outcomes

To analyze changes in circadian parameters, including DLMO, Phase Angle Difference, inter-daily stability, and intra-daily variability, multilevel mixed-effects models will be employed. The fixed effect’s structure will incorporate time (*Baseline vs. Post-treatment*), and the interaction between time and treatment condition (*Light@Home*,* LightCafé*, and *LightCafé* +). Inclusion of random intercepts for participants and study site and random slopes for time within participants will be evaluated based on model fit criteria, including AIC and BIC. Circadian effects will be compared between timepoints by evaluating the fixed effect of time in the model, while the effect of the treatment condition will be interpreted by assessment of the interaction term between time and treatment condition.

Following the assessment of changes in circadian parameters (e.g., DLMO, Phase Angle Difference, inter-daily stability, and intra-daily variability), multilevel mediation analyses will be conducted to determine whether these changes mediate the relationship between timepoint and depressive symptoms (QIDS-SR). Each mediator will be tested individually using an approach based on Bauer et al. [99] which includes decomposing within- and between-person components to yield valid indirect effect estimates in nested data. We will apply bootstrapping (5000 samples) to estimate the indirect path (ab) and construct 95% confidence intervals for each mediator. In addition, moderation analyses will examine whether baseline depression severity or sleep quality interact with treatment conditions to affect depressive outcomes. Results will report direct effects (c′), indirect effects (ab), and any interaction effects (a × b), along with the corresponding confidence intervals and *p*-values.

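### The pooled pre-post effect on DLMO and sleep timing has no stated term for a civil clock change, which year-round recruitment would place inside roughly 12–19% of measurement pairs

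*Protocol article*

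**What the plan says.** The general eligibility criteria exclude people who "Have travelled across more than one time zone in the past month or during the treatment period". This is the only provision in the article that concerns a shift of the time base. Civil clock changes are not mentioned.

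Under Recruitment {15}: "We intend to include participants year-round for approximately 2 years".

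Under Circadian rhythm parameters, DLMO is defined as the time at which melatonin crosses a threshold. The saliva sample-size section simulates it as a clock time, "with a mean DLMO set at 23:00 and extensive between-person variance" (SD 120 min) and a within-person SD of 45 min. It claims 96.40% power with 72 participants "to detect a phase shift of 30 min in DLMO with an alpha level of 0.05".

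In the circadian analysis, the fixed effects are time and time by condition. On interpretation the plan says: "Circadian effects will be compared between timepoints by evaluating the fixed effect of time in the model". The sleep-parameter models treat "midsleep timing, sleep onset, and sleep offset" as outcomes over days since treatment start. They include a weekend/weekday factor, but nothing for a change of clock.

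**The concern.** All three arms receive bright light, so nothing subtracts a calendar shift from the pooled time effect. If the clocks change between the baseline DLMO session (M1) and the post-treatment session (M3), a participant whose biological phase has not moved shows a different clock time. When the clocks go back, an unchanged DLMO reads earlier, which is the direction of the phase advance that the background section attributes to morning light. When they go forward, it reads later.

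Three kinds of result are exposed:
- the pooled pre-post change in DLMO;
- the sleep onset, sleep offset and midsleep trajectories, where a clock change is a step inside the participant's series;
- analyses that use each person's own DLMO change, namely the mediation of timepoint on QIDS-SR through circadian change and the regressions linking DLMO change to brain change.

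The second and third follow individual displacements directly.

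**Working it through.** **Inputs from the article.** Saliva n = 72; within-person SD 45 min; target mean shift 30 min; alpha 0.05. M1 falls in the extra week that begins two weeks before treatment. M3 falls in the first week after one to three weeks of treatment.

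**Assumptions not in the article.** Two one-hour civil clock changes a year in opposite directions; even enrolment over the year; a two-sided test; and, as the worst case, no re-entrainment.

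**1. The plan's own power.** With two timepoints, a random-intercept model is a paired comparison.
- SD of change = 45 × √2 = 63.6 min; SE = 63.6/√72 = 7.5 min.
- Normal power = Φ(30/7.5 − 1.96) = Φ(2.04) = 97.9%; noncentral t gives 97.6%.

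This agrees with the stated 96.40% to within two points. A 30-min contrast between two arms of 24 would have about 37% power. The powered quantity is therefore the pooled pre-post change, which is the exposed one.

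**2. Share of pairs that straddle a change.** Count the first treatment day as day 0. M1 lies on days −14 to −8. M3 lies between day 7 (one treatment week) and day 27 (three weeks).
- Extremes: 7 + 8 = 15 days to 27 + 14 = 41 days.
- In whole weeks, the gap is typically 3 to 5.
- Share p = 2 × gap/year: 6/52.18 = 11.5% to 10/52.18 = 19.2%, or 8 to 14 of 72.
- At the extremes: 30/365 = 8.2% to 82/365 = 22.5%, or about 6 to 16 of 72.

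Sleep monitoring runs over the baseline week, one to three treatment weeks and one further week. That is again 3 to 5 weeks, so a similar share of those series contains a change.

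**3. Spring and autumn balanced.** The mean displacement is 0. The variance ratio is 1 + p × 60²/63.6² = 1 + p × 3600/4050.
- 3 to 5 weeks: 1.10 to 1.17, so the SE rises by 5 to 8%.
- 15 to 41 days: SD of change 65.9 to 69.7 min; power for 30 min 96.8% to 95.0%; simulated type I error about 5% (20,000 runs).
- If re-entrainment leaves only a 30-min residual, the ratio is 1 + p × 900/4050 = 1.03 to 1.04 for 3 to 5 weeks.

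**4. Only one of the two changes sampled.** Half of p is displaced in one direction, so the mean shift is 60 × p/2.

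| M1–M3 gap | p | Mean shift | Type I error of pooled test |
|---|---|---|---|
| 15 days | 8.2% | 2.5 min | 6% |
| 28 days | 15.3% | 4.6 min | 9% |
| 41 days | 22.5% | 6.7 min | 13% |

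With a 30-min residual the mean shifts are half as large.

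**5. Between arms.** Allocation is randomised and stratified by melatonin participation, so straddlers have the same expected share in each arm. Simulated type I error of a 24 versus 24 contrast with balanced directions stayed at about 5%.

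**The case against.** A reader might set the 60-min displacement beside the 30-min target and infer that the artefact is twice the effect the sub-study is powered for. The documents do not support that. Sixty minutes is the most one participant's value can move, while 30 min is a group mean. The mean would move by 30 min only if a net half of the participants were displaced the same way, and by 60 min only if all were. Large one-directional shares are not supported either: 12–19% is the total over two changes of opposite sign.

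The time-zone criterion might also look like the source of the problem. It is not. A one-zone trip with return restores the home clock, saliva is collected at home, and tolerating one zone contradicts nothing else in the plan. That criterion does not govern the civil clock change, which produces every figure above.

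Other points on that side carry weight:
- Recruitment for about two years from February 2024 would, on the same civil-time assumption, include two spring and two autumn changes, which favours balance.
- Sleep times partly follow work, social obligations and sessions at fixed clock hours, so many participants may have adapted by the second measurement.
- The stated aim of saliva sampling is a comparison between conditions, which randomisation protects.
- Time-base rules may stand in the full protocol or analysis plan, which are not shown.

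These points limit the size of the problem but do not remove it. The article itself fixes the circadian model and says that change over time is read from the uncontrolled time effect. It names a day-type factor for sleep but none for a clock change. Equal spring and autumn numbers are not guaranteed in a trial that also enrols seasonal depression, although the article gives no seasonal enrolment figures.

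**Conclusion.** The point holds in a narrow form. The pooled pre-post effects on clock-time outcomes, and the analyses of individual DLMO change, are open to a calendar artefact that the stated models do not separate from treatment. With spring and autumn balanced, it costs a little precision and no validity. With only one change sampled, it moves the pooled DLMO mean by about 2.5–6.7 min and raises type I error to about 6–13%. Both are worst cases for re-entrainment, and all figures rest on the assumed clock changes and even enrolment.

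Comparisons between arms are unbiased and gain only noise. The DLMO-to-sleep-onset phase angle is a difference of two times on the same clock, so the label cancels. The MADRS primary outcome is not a clock time. This is an inexpensive improvement to secondary, mechanistic analyses and does not threaten the trial's main conclusion.

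**What to change.** - In the circadian and sleep-parameter models, add an indicator derived from assessment dates (no change, clocks back, clocks forward between the measurements compared), interacted with time. The time effect for participants without a change is then the treatment-related estimate.
- Analyse all times in one documented time base. This alone is not enough: for someone who has already adapted to the new clock, a fixed base would itself create an apparent 60-min shift. The indicator absorbs the displacement in either case.
- Repeat the pooled DLMO, sleep-timing, mediation and DLMO–brain results without the straddling pairs, and report any difference.

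The cost is two degrees of freedom and one extra sensitivity analysis, using dates already collected. The plan allows minor, documented modifications. The travel criterion need not be reworded and saliva starts need not be blocked around clock changes, because little benefit from either can be shown.

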#### MRI Assessment Criteria

For participants undergoing Magnetic Resonance Imaging (MRI) assessments, additional criteria apply:

Individuals with claustrophobia, a history of neurological disorders, or foreign non-MRI compatible metal objects in or on their body are ineligible for MRI assessments.

Participants not meeting the MRI eligibility criteria can still participate in the broader trial, provided they meet the general participation criteria.

#### Eligibility of the research team

BLT will be administered by trained clinical professionals, including psychologists, nurses, and social workers, with assistance from master’s-level students. The assessment of the primary outcome will be conducted by blind raters, who will either be psychologists or master’s-level psychology students.

#### Who will take informed consent? {26a}

All patients referred to BLT at the study centers are invited to participate in the study. Those expressing interest receive information via email. A follow-up phone call is conducted to confirm their interest and schedule an intake appointment. During the intake, a member of the study team goes over the information letter and informed consent document in detail and answers any questions. If a patient decides to participate, they sign the informed consent and proceed with the diagnostic interview.

#### Additional consent provisions for collection and use of participant data and biological specimens {26b}

In addition to providing consent for participation in the trial, participants are offered the opportunity to grant separate consent for specific aspects related to their data and biological specimens. These supplementary consent provisions encompass:

The permission for data retention for a minimum of 15 years and the potential use in future researchThe choice to allow or prohibit recording of clinical interviews,The decision to participate or abstain from saliva collection, andThe consent that the brain scan is not a medical sequence, but if an incidental finding is detected (any brain abnormality), the hospital will inform the general practitioner and the patient.

Participants may accept or decline these provisions without any impact on their eligibility for the trial, thus ensuring participants’ autonomy in the utilization of their data and specimens.

## Interventions

### Explanation for the choice of comparators {6b}

This study compares the effectiveness of three distinct BLT administration strategies for treating depression:

I.**Home-Based BLT (*****Light@Home*****)**: Patients receive BLT in their own homes.II.**BLT in LightCafé (*****LightCafé*****)**: Patients undergo BLT in a café-like environment (*LightCafé*), which emphasizes lifestyle improvements alongside the therapy.III.**Personalized BLT in the LightCafé (*****LightCafé +*****)**: Patients receive BLT in the *LightCafé*, with treatment timing tailored to their individual sleep–wake pattern and personalized timing of darkness with the use of BBG.

The *Light@Home* condition serves as an active control condition against which both other conditions will be evaluated. Given that our primary objective is not to measure the effectiveness of BLT in alleviating depressive symptoms per se, but rather to optimize its delivery, the inclusion of a placebo or treatment-as-usual condition in this trial is deemed unwarranted. To assess and possibly control for the difference in expectations of treatments, all participants will complete the Credibility/Expectancy Questionnaire (CEQ; [71]) before treatment onset.

### Intervention description {11a}

In all study arms, participants are subjected to BLT in adherence to Dutch BLT guidelines [72], utilizing an Innolux LED light Lamp delivering light with an illuminance of 10,000 lx at a distance of 70 cm and a color temperature of 3800 K. BLT sessions, lasting 30 min each, are scheduled from Monday to Friday between 7:30 AM and 10:30 AM.

The number of BLT sessions is contingent upon the individual response of each participant, with a maximum duration of 3 weeks. Initially, participants undergo five consecutive BLT sessions during the workweek. Subsequently, the therapeutic efficacy is evaluated utilizing the QIDS-SR during the Friday session. If the QIDS-SR falls below 6, remission is inferred, leading to the termination of BLT. Alternatively, an additional five sessions are administered. This evaluation and decision process is repeated at the end of the second week. If the QIDS-SR score is still above 6, a third and final week of treatment is provided.

This individualized strategy is intended to reduce the small risk of (hypo)manic switches, which occur in less than 2% of bipolar patients and almost exclusively in those not maintained on mood stabilizers [11, 73]. We will continuously monitor for (hypo)manic symptoms using the Young Mania Rating Scale (YMRS; [74]) and clinical observation: a YMRS score ≥ 13 and clinician‐identified symptoms will lead to immediate treatment cessation, while scores of 10–11 will prompt a joint review with a second clinician to decide on discontinuation [75, 76].

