**Fig. 2 Fig2:**
[figure not shown]
This figure presents a schematic overview of the study design. The study is divided into three phases: Baseline, Treatment, and Follow-up. Participants receive Bright Light Therapy from Monday to Friday, with the option to repeat the treatment up to three times if the score on the Quick Inventory of Depressive Symptomatology – Self-report (QIDS-SR; [70]) remains higher than 6. Gray-colored areas in the figure represent optional parts of the study protocol. EMA; Ecological Momentary Assessment

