### Treatment phase

During the treatment phase, participants receive 1, 2, or 3 weeks of BLT within their assigned condition. Every Friday, depressive symptoms are assessed using the QIDS-SR, regardless of whether the participant received treatment that week. Treatment will be continued as long as QIDS-SR-score is higher than 6, with a maximum of 3 weeks. Treatment tolerability and mania symptoms are assessed using the YMRS after each week of BLT. EMA, actigraphy, and light logger usage continue throughout the treatment.

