### Secondary Study Outcomes

#### Subjective Assessment of Depressive Symptoms, Relapse Rates and Functional Outcomes

Multilevel mixed-effects models will be constructed to assess depressive symptom improvement, measured weekly during therapy and at follow-up assessments using the QIDS-SR scores as the dependent variable. Fixed effects will include timepoint as an categorical variable (baseline, 1 week, 2 weeks, 3 weeks, 4 weeks, 10 weeks, and 4 months), and the interaction between timepoint and treatment condition (*Light@Home*,* LightCafé*, and *LightCafé* +). Random intercepts and slopes will be included for participants and study centers, as well as random slopes for time within participants, based on model fit criteria. Confounding variables (age, sex, clinical diagnosis, and credibility/expectancy of treatment) will also be evaluated and included as necessary. A variable will be added to account for treatment duration (1 week, 2 weeks, 3 weeks). Similar models will be considered for analyses of relapse rates, functional outcome, and Quality of Life with inclusion of the respective timepoints as fixed effects (see Table 1).

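### At a QIDS-SR of exactly 6 the protocol both continues and ends light therapy, and its YMRS action bands skip a score of 12

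*Protocol article*

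**What the plan says.** **QIDS-SR.** Four statements in the protocol article govern how long treatment lasts.

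- Intervention description {11a}, first rule: "If the QIDS-SR falls below 6, remission is inferred, leading to the termination of BLT". The other branch is: "Alternatively, an additional five sessions are administered". For the next decision: "This evaluation and decision process is repeated at the end of the second week".
- Intervention description {11a}, the sentence that follows: "If the QIDS-SR score is still above 6, a third and final week of treatment is provided".
- Fig. 2 legend: treatment may be repeated if the score "remains higher than 6".
- Treatment phase: "Treatment will be continued as long as QIDS-SR-score is higher than 6, with a maximum of 3 weeks".

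Eligibility criteria {10} uses the same scale and takes a score of 6 or more as a sign of a current depressive episode.

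**YMRS.** Section {11a} also sets two action bands. At 10–11, two clinicians jointly decide whether to stop. At 13 or more, treatment stops at once; the text links this score to clinician-identified symptoms with the word 'and'. Section {11b} allows discontinuation for mania symptoms on the YMRS 'or' on clinical assessment, and gives no cut-off.

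**The concern.** The QIDS-SR is an integer scale and 6 is the boundary at which each weekly decision is taken. If one statement stops only below 6 and another continues only above 6, a patient at 6 has two opposite instructions. What is at stake is the dose: 5, 10 or 15 sessions. The same rule feeds the three-level treatment-duration variable in the QIDS-SR models. Treatment is given by two institutions with several LightCafé locations, so the two wordings could be applied differently in different places.

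The YMRS bands belong to a safety rule in a trial that admits bipolar patients and has no data monitoring committee. Taken literally, a score of 10 or 11 triggers a review while the worse score of 12 triggers nothing.

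**Working it through.** No published figure needs reproducing. The check takes every integer score through each stated rule.

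**Step 1: one QIDS-SR decision (range 0–27).**

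| Score | First rule in {11a} (stop if < 6) | Third-week sentence in {11a}, Fig. 2 legend, Treatment phase (continue if > 6) |
|---|---|---|
| 0–5 | stop | stop |
| 6 | continue (6 is not < 6) | do not continue (6 is not > 6) |
| 7–27 | continue | continue |

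The conflict lies at one score. After week 1 it is {11a} against the Fig. 2 legend and the Treatment phase section. After week 2 it also lies inside {11a}, because the repeated first rule and the third-week sentence disagree.

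**Step 2: total sessions.** Each week has five sessions, with a maximum of three weeks. Three readings are possible:

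- A: stop below 6 at both decisions.
- B: continue only above 6 at both decisions.
- H: {11a} read sentence by sentence, that is, stop below 6 after week 1 and continue only above 6 after week 2.

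| Week 1 score | Week 2 score | A | H | B | A − B |
|---|---|---|---|---|---|
| 6 | below 6 | 10 | 10 | 5 | 5 |
| 6 | 6 | 15 | 10 | 5 | 10 |
| 6 | above 6 | 15 | 15 | 5 | 10 |
| above 6 | 6 | 15 | 10 | 10 | 5 |

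All other score pairs give the same total under A, H and B. Under B a patient at 6 after week 1 has already stopped, so the week 2 score in the first three rows matters only for A and H. The table does not assume that treatment leaves that score unchanged.

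**Step 3: number of patients.** The article does not say how often a score of exactly 6 occurs on a decision Friday, so no count can be given. For scale only, each 1% of patients is 0.01 × 231 = 2.31 of those enrolled, or 0.01 × 210 = 2.10 of those in the power calculation.

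**Step 4: YMRS (range 0–60).** Scores 0–9: no band. Scores 10–11: joint review. Score 12: no band. Scores 13–60: cessation. The gap is one score, between two bands that both trigger action. The 'and' in {11a} allows two readings at 13 or more: either the score and the clinical symptoms must both be present, or each is a trigger. Only the second agrees with {11b}.

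**The case against.** The strongest reply is that this is loose drafting at one integer. None of the three continuation statements contains the word 'only'. The wording is the same for all arms, so no bias between arms has been shown, and the duration variable can be recorded correctly whichever rule was used. A YMRS of 12 is not unprotected: {11a} pairs the scale with clinical observation, and {11b} lets staff stop treatment on clinical assessment or in the patient's interest. The 'and' in {11a} may simply list two triggers.

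Most of this stands and limits the severity. It does not remove the contradiction. Continuing as long as the score is above 6 naturally means not continuing at 6, and the article states the rule four times with two different cut-offs, so this is not detail left to a fuller document.

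Two stronger readings are tempting. First, a reader might infer that the conflict leaves open whether 6 counts as remission, and so disturbs the time-to-remission analysis. The documents do not support that. Only {11a} defines QIDS-SR remission, as below 6, and the entry criterion agrees with it; the other statements concern continuation. An effect through censoring would need treatment duration to mean each patient's own duration, which is not stated and may be settled in an analysis plan. Stopped patients are in any case still measured: "Every Friday, depressive symptoms are assessed using the QIDS-SR, regardless of whether the participant received treatment that week". Second, a reader might infer damage to the primary result. The MADRS analysis is defined without reference to this cut-off.

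**Conclusion.** The concern holds as a contradiction in the text. A patient scoring exactly 6 on a decision Friday has opposite instructions and could receive 5 or 10 fewer sessions, out of at most 15, depending on the section followed. The 10-session difference arises only between readings A and B, for a score of 6 after week 1 and 6 or more after week 2. Reading {11a} sentence by sentence gives intermediate totals for some patterns. The number of patients affected is unknown.

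The definition of the primary MADRS analysis, the sample size and the QIDS-SR remission definition are unaffected. The YMRS gap at 12 and the unclear 'and' are real but secondary, because clinical judgement covers them. The conclusion assumes that the three continuation statements carry their ordinary meaning. The text is wrong as written; severity is minor to should-fix.

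**What to change.** 1. Enrolment is under way (Trial status), so first establish which QIDS-SR rule each site applies, and record the rule used for patients already treated.
2. State one cut-off in {11a}, the Fig. 2 legend and the Treatment phase section. The preferred rule is to stop below 6 and continue at 6 or higher, because it matches the remission definition in {11a} and the entry threshold in {10}. The clinical team should confirm it, since {11a} gives limiting (hypo)manic switches as a reason for the individualised duration.
3. For the YMRS, set joint review at 10–12, and cessation at 13 or more or on clinician-identified (hypo)manic symptoms, in line with {11b} and again subject to clinical confirmation.

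The cost is a small amendment, a query to the sites and a check of the electronic case report form. If sites have continued only above 6, the preferred rule gives future patients who score 6 up to 5 or 10 more sessions, and this change during the trial must be documented. The sample size and the primary analysis need no change.
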